#### ***Patient level***

A logistic regression analysis will analyse changes in the rates of patient admissions with adverse events and complications between before-and-after measurements, while correcting for clustering on the hospital department level. The intra-class correlations, the ratio of the between group, and the total variance will be calculated. Since the patient records will be different in the before–and-after measurements, the effect of timing (i.e. auditing) will be accounted for with a fixed effect for time (dummy variable for the second measurement). The incidence rates of adverse events and complications will be calculated with 95% confidence intervals (CIs). The inter-rater agreement within pairs of physicians will be expressed as a kappa (K) statistic with 95% CIs and as a percentage of records that agree about the presence or absence of complications and adverse events.

A linear mixed model will be used to analyse the before-and-after outcomes of the quality of hospital care according to the patients. To account for the possibility that changes over time will be influenced by changes in patient mix, terms will be added to the model for age, sex, education, and self-reported general and mental health status. Since the patients will be different in the before-and-after measurements, the effect of the timing of the auditing will be accounted for with a fixed effect for time (dummy variable for the second and third measurements).

We will use a linear mixed model with a Poisson distribution for the SMR and prolonged hospital stay to compare the rates from baseline to the end of the initial 18-month evaluation period (3 months before and 15 months after auditing). We will adjust this model for patient and departmental characteristics.

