### Outcomes

We measure several outcomes at the patient, professional, and department levels (Table 4). The primary outcomes are adverse events and complications. The secondary outcomes are patient experiences, the standardised mortality rate (SMR), prolonged hospital stay, team climate, and patient safety culture. These outcomes are assessed using medical record reviews, questionnaires, routine hospital administrative data, and observations. We collect data 3 months before the audit and will collect data again 15 months afterwards. We measure patient experiences also 9 months after auditing; the SMR and prolonged hospital stay are generated from the routine administrative hospital data monthly.

**Table 4 T4:** Methods and instruments for measuring the effects of auditing

**Outcome variable**	**Data source**	**Frequency (type) of measurement and sample size per measurement**	**Moments of measurement**	**Unit of analysis**

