We will measure two patient safety indicators: SMR and prolonged hospital stay. The SMR is a method for comparing mortality ratios over time, or between subpopulations, taking into account the differences in population structure [39]. The ratio is of the observed to expected deaths, conventionally multiplied by 100. A prolonged hospital stay is the actual hospital stay of a clinically admitted patient that is more than 50% longer than expected [40]. A prolonged hospital stay takes into account the fact that patient stays tend to become prolonged after complications [41]. The SMR and hospital stay data are generated from the routine administrative data of the hospital.

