To decrease response bias, non-respondents receive a reminder. Missing values in the medical record review are checked. Inter-rater agreement of retrospective assessments is measured and given back to the physician reviewers to improve the reliability of the assessment of adverse events and complications.

Information bias is reduced by having a research assistant enter the research data. The data will be separated from the names of the participants (departments, healthcare providers, and patients). Each participant will be identified in the database with a number and an identity code. These codes will be available only to the research assistant and researchers. An independent researcher will check the data entries. An independent statistician will check the analyses.

To prevent confounding bias, we will study potentially confounding determinants of the relationship of auditing and patient safety by means of regression analysis and time series analyses.

To prevent publication bias, the study has been registered in the Dutch register for clinical trials. Additionally, we have installed an external Advisory Board with the special tasks of checking the integrity of the study group and giving methodological feedback.

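### The primary before-after model has department clustering and a time term but no patient case-mix terms, although the secondary patient outcomes are adjusted for patient characteristics

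*Protocol article*

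**What the plan says.** Under Outcomes, the Protocol article states: "The primary outcomes are adverse events and complications". Under Statistical analyses, Patient level, the analysis is given as "A logistic regression analysis will analyse changes in the rates of patient admissions with adverse events and complications between before-and-after measurements". Departments enter this model through a qualifying clause: "while correcting for clustering on the hospital department level". The next step is introduced with "Since the patient records will be different in the" two measurements, and the consequence drawn is that "the effect of timing (i.e. auditing) will be accounted for with a fixed effect for time (dummy variable for the second measurement"). No other fixed effect and no patient covariate is named for this model.

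The following paragraphs of the same section treat the secondary patient outcomes differently. For patient experiences: "To account for the possibility that changes over time will be influenced by changes in patient mix, terms will be added to the model", and the terms listed are age, sex, education and self-reported general and mental health. The Poisson model for the standardised mortality ratio (SMR) and prolonged stay is adjusted for characteristics of patients and departments. The SMR is already standardised by construction: "The ratio is of the observed to expected deaths, conventionally multiplied by 100".

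On confounding in general, the Discussion says: "we will study potentially confounding determinants of the relationship of auditing and patient safety by means of regression analysis and time series analyses". It also acknowledges that there is no concurrent control group.

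**The concern.** The plan accepts that the two samples contain different patients, and it names change in patient mix as something that can distort a comparison over time. It acts on this for the secondary patient outcomes and not for the primary one. In an uncontrolled design, the coefficient of the time dummy takes up every change between the two periods. If patients within a department become older, sicker or more often acutely admitted, that change enters the estimated audit effect on adverse events and complications. The bias can run either way: a worsening mix can hide a benefit, and an improving mix can imitate one.

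**Working it through.** **1. What the plan adjusts for, outcome by outcome** (Statistical analyses, Patient level)

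| Outcome | Different patients acknowledged | Department | Patient terms |
|---|---|---|---|
| Adverse events and complications (primary) | yes | clustering correction | none named |
| Patient experiences | yes | mixed model | age, sex, education, self-reported general and mental health |
| SMR, prolonged stay | not stated | mixed model, departmental characteristics | patient characteristics; both measures also use an expected value |

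**2. What the rest of the design covers**

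- Sampling: 50 records × 8 departments = 400 per measurement, which agrees with Table 4. Equal numbers per department in both periods block a shift between specialties.
- Clustering correction: handles stable differences between departments, not change inside one.
- Random selection of patients (Discussion): makes each sample representative of its own period. It does not balance the two periods.
- Time series: planned only for SMR and prolonged stay. The primary outcome has two time points, at −3 and +15 months, so 3 + 15 = 18 months apart.

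What remains uncovered is case-mix change within departments over about 18 months.

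**3. The plan's own figure.** Sample size and precision calculation states a precision of 7% for the before-after difference. With independent records the 95% half-width is 1.96 × √(2p(1−p)/400). It is 2.4 points at p = 3%, 4.2 at 10%, 5.2 at 17% and 6.9 at 50%. To reach 7 points, the variance would have to be inflated by (7/half-width)², about 8.8, 2.8, 1.8 and 1.02 respectively. No event rate, intra-class correlation or before-after correlation is given, so 7% can be neither confirmed nor refuted. The point here does not depend on it.

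**4. How large the bias could be (all inputs assumed, no true audit effect).** Crude rate = (share low-risk × risk low) + (share high-risk × risk high).

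- Risks 8% and 16%, high-risk share 40% before and 50% after: 0.6 × 8% + 0.4 × 16% = 11.2%; 0.5 × 8% + 0.5 × 16% = 12.0%. The shift is 0.8 points, or 0.8/11.2 = 7% relative. Against 7 points of precision it is 0.8/7, about one-ninth.

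A second set starts from a 30% high-risk share and uses a threefold risk ratio. With δ the shift and SE = √(p₁(1−p₁)/400 + p₂(1−p₂)/400), the false-positive rate of a two-sided 5% test is 1 − Φ(1.96 − δ/SE) + Φ(−1.96 − δ/SE). Clustering is ignored.

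| Risks low/high | Rise in high-risk share | Crude rate | Odds ratio | False-positive rate |
|---|---|---|---|---|
| 5% / 15% | 10 points | 8.0% to 9.0% | 1.14 | 8.0% |
| 10% / 30% | 10 points | 16% to 18% | 1.15 | 11.7% |
| 5% / 15% | 20 points | 8.0% to 10.0% | 1.28 | 16.7% |
| 10% / 30% | 20 points | 16% to 20% | 1.31 | 31.4% |

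Worked for the first row: 0.7 × 5% + 0.3 × 15% = 8.0%; 0.6 × 5% + 0.4 × 15% = 9.0%; SE = √(0.000184 + 0.000205) = 0.0197; δ/SE = 0.01/0.0197 = 0.51.

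**5. Room for covariates.** The Background gives adverse events in 3% to 17% of admissions worldwide: 400 × 0.03 = 12 and 400 × 0.17 = 68 events per period. Counting complications would add to this.

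**The case against.** The strongest reply rests on the Discussion. Its sentence on confounding promises regression analysis and time series. Time series belong to SMR and prolonged stay, and in the Statistical analyses section the only patient-level method called a regression is the primary logistic model. The sentence may therefore have been meant to cover adverse events, with the covariate list left to a fuller document. A reader might infer from the model description that the plan has ruled out case-mix adjustment of the primary outcome. The document does not support that. It does fix a model without such terms, and the sentence in the Discussion names no outcome, model or covariate that would change it. The reply lowers certainty but does not remove the problem, because the article gives the patient-mix rationale and covariates for another outcome in the same section.

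A reader might also infer that the comparison rests on a time dummy alone. It does not: department clustering is corrected, and the fixed number of records per department closes off the most obvious route for drift in a multi-specialty hospital. That part of the reply stands in full.

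Finally, moderate drift produces a bias well inside the stated precision, and the document gives no evidence that drift occurred. That stands too. The larger false-positive rates need a 20-point shift and a threefold risk ratio, both assumed.

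**Conclusion.** The point holds in limited form. As written, the primary estimate is open to within-department case-mix change over about 18 months, and the plan treats its primary outcome less carefully than its secondary patient outcomes. This should be changed, but it does not invalidate the study. Certainty is moderate, given the general statement in the Discussion.

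The size of the bias cannot be derived from the document. On assumed strata, a 10-point shift in high-risk share gives an odds ratio of about 1.14 to 1.15 with no true effect, and a 20-point shift about 1.28 to 1.31.

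It would go too far to say that adjustment would remove the confounding. It reduces bias from measured case mix. Secular trends and the other hospital safety initiatives that the Discussion acknowledges would remain.

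**What to change.** In Statistical analyses, Patient level, add a small pre-specified set of case-mix covariates to the primary logistic model, taken from the reviewed record or the administrative data. Examples are age, sex and acute versus elective admission. Choose variables fixed at admission, so that adjustment cannot absorb an effect of the audit itself. A single expected-risk score could replace several terms if one can be linked to each sampled admission. The Outcomes section shows that expected deaths and expected stay are used, but not that per-admission values are held or linkable, so this must be checked first.

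Report the crude estimate beside the adjusted one. Add one sentence stating that the confounder regression announced in the Discussion applies to the primary outcome, and with which terms.

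The cost is extracting or linking a few variables for 400 records per measurement, plus a few parameters in a model with limited events (about 12 to 68 adverse events per period, more with complications). The set must therefore stay small.

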### Sample size and precision calculation

With a sample of 50 medical records of patients from each of the eight hospital departments, we can estimate the difference in preventable adverse events and complications before and after auditing with a precision of 7%. The precision calculation of this study is based on Zegers et al. [42] and accounts for clustering in the before-and-after measurements. Since the patient records were drawn from the same departments, there will be some similarity in the before and after groups, i.e. a correlation between the before group and the after group.

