#### ***Professional and team level***

To account for the influence of department type on team climate and patient safety culture, we will analyse the before-and-after outcomes using a linear mixed model with the department type as a random effect. Since the professionals are almost the same in the before-and-after measurements, the difference scores in team climate and patient safety culture will be considered as dependent variables.

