#### ***Departmental level***

The paired *t*-test (by department) will be used on the percentage of observed patient safety data collected during safety walk arounds to measure difference in patient safety on departments before and after auditing.

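### The primary before-after model names one common time effect and no variation in change between the eight departments, so the interval for the audit effect may be too narrow

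*Protocol article*

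**What the plan says.** Statistical analyses, Patient level: admissions with adverse events and complications are compared before and after by logistic regression, corrected for clustering by department. An intra-class correlation (between-group over total variance) is to be reported, and "the effect of timing (i.e. auditing) will be accounted for with a fixed effect for time (dummy variable for the second measurement". The reason given for the dummy is that different records are sampled at each measurement. The patient-experience outcome gets a linear mixed model with case-mix terms and fixed dummies for the second and third measurements; its random effects are not named. The Poisson model for the standardised mortality ratio (SMR) and prolonged stay names no time term.

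Other outcomes are handled differently. Staff surveys use difference scores in a "linear mixed model with the department type as a random effect". A paired t-test by department "will be used on the percentage of observed patient safety data collected during safety walk arounds".

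Sample size and precision calculation: "With a sample of 50 medical records of patients from each of the eight hospital departments", the difference is to be estimated "before and after auditing with a precision of 7" per cent. The calculation is said to be one that "accounts for clustering in the before-and-after measurements", because "there will be some similarity in the before and after groups, i.e. a correlation between the before group and the after group". No event rate, intra-class correlation or before-after correlation is given.

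**The concern.** The most natural reading of a clustering correction with a single variance ratio is a random department intercept. That intercept describes how departments differ in level, and it largely cancels when each department is compared with itself. The precision of a before-after contrast depends instead on how much the change varies between departments, and no term for that is named.

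Such variation is likely here. Each department head draws up and carries out a separate improvement plan (Auditing of patient safety). Audits are spread from October 2011 to April 2013 (Study design and setting), so the before and after windows fall at different calendar times. The Discussion acknowledges other safety initiatives in the hospital. With no concurrent controls, a department-specific shift from any cause enters the estimated audit effect. If the standard error leaves out this source, chance shifts in a few departments can look like an effect of auditing on the primary outcome.

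**Working it through.** **Inputs from the Protocol article.** Eight departments with 50 records each per measurement, so 8 × 50 = 400 per measurement. The planned confidence level for incidence rates is 95% ("The incidence rates of adverse events and complications will be calculated with 95% confidence intervals (CIs"). The Background gives adverse-event rates of 3% to 17% worldwide, as context only.

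**Assumptions.** τ, the SD between departments of the before-after change in log-odds: 0, 0.3 and 0.5. Event rate p: 10% to 30%. Rates above 17% are included because complications are counted too.

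**1. The plan's own figure.** Half-width = 1.96 × √(2p(1−p)/400 × D), where D is the variance factor for clustering. With D = 1 this gives 4.16 points at p = 10%, 5.21 at 17%, 6.35 at 30% and 6.93 at 50%. To reach 7 points, D must be 2.83, 1.81, 1.21 and 1.02 respectively. With 50 records per department, intra-class correlation ρ and before-after correlation r of department effects, D = 1 + 49ρ − 50ρr. A common effect in all departments means r = 1, so D = 1 − ρ, which is below 1. Since p, ρ and r are not given, the 7% can be neither reproduced nor refuted.

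**2. Rejection rate by hand.** The sampling variance of one department's log-odds change is about v = 2/(50p(1−p)). Its full variance is v + τ². A model without the second part understates the standard error by k = √((v + τ²)/v), and the true rejection rate of a nominal 5% test is 2[1 − Φ(1.96/k)].

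| p | v | τ = 0.3: k, rejection | τ = 0.5: k, rejection |
|---|---|---|---|
| 12% | 0.379 | 1.11, 7.8% | 1.29, 12.8% |
| 20% | 0.250 | 1.17, 9.3% | 1.41, 16.6% |
| 30% | 0.190 | 1.21, 10.6% | 1.52, 19.7% |

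At τ = 0, k = 1 and the rate is 5%.

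**3. Simulation under no average effect** (2000 studies per setting). A department-stratified Mantel-Haenszel test stands in for the intercept-only logistic model.

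| p | τ = 0.3 | τ = 0.5 |
|---|---|---|
| 12% | 7.9% | 16.0% |
| 20% | 8.4% | 20.2% |
| 30% | 10.4% | 18.9% |

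At p = 12% and τ = 0 the rate is 4.6%. A paired t-test on the eight department differences gives 4.4% to 5.4% throughout.

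**4. Coverage of a nominal 95% interval** (1000 studies per setting, log-odds effect −0.3, SD of department intercepts 0.4). The first two columns use a logistic model with department intercepts and one time dummy.

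| τ | Common effect, p = 10% | Common effect, p = 30% | Robust, normal reference (both p) | Robust, t on 7 df (both p) |
|---|---|---|---|---|
| 0 | 95.3% | 95.1% | 92-93% | 96% |
| 0.3 | 92.1% | 88.7% | 91% | 95-96% |
| 0.5 | 85.1% | 81.3% | 89-90% | 94-95% |

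The paired t on department log-odds differences covers 94% to 96% throughout.

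**5. Cost of the t reference.** 2.36/1.96 = 1.21, so about 21% wider even at τ = 0.

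**The case against.** The strongest reply is that the clustering method is not named. A fixed time effect gives the mean change and does not exclude a random time slope, and the correction could be generalised estimating equations or robust errors. A condensed article may leave this to the analysis plan. This stands against any claim that the model is certainly intercept-only, and it stands more strongly for patient experience, where no random effects are named. It does not dispose of the point: robust errors with a normal reference also under-cover with eight departments, so a small-sample reference is needed under either reading.

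Second, the SDs are assumed, and with no heterogeneity coverage is correct. This stands.

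Third, the departments were chosen for estimated high risk and the Discussion concedes low generalisability. If inference is confined to these eight, true differences in audit effect need not enter the interval. That is correct for the audit effect itself. Department-specific shifts unrelated to auditing, however, remain noise in an uncontrolled comparison even for a fixed set of departments. The article also asks whether auditing improves safety in hospitals generally and plans recommendations for others.

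Fourth, the paired t-test for walk arounds is no inconsistency in itself, because the department is the unit there (n = 8). This stands. The staff-survey model is the closer comparison.

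A reader might also infer that clustering is ignored and the records are treated as independent. The article does not say this: both the analysis and the precision section invoke clustering.

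**Conclusion.** The point holds in conditional form for the primary model and, as far as it is specified, the patient-experience model. The stated audit effect is one common time effect, with no department-by-period variation and no reference suited to eight departments. The interval may therefore be too narrow. Under assumed SDs of 0.3 and 0.5, a nominal 5% test rejects about 8-10% and about 15-20% in simulation; the hand formula gives 8-11% and 13-20%. With an SD of 0 nothing is lost.

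Three stronger readings are tempting and not supported. The intervals cannot be called too narrow outright, because the heterogeneity is not quantified and the clustering method is not named. The point does not extend to the SMR and prolonged-stay model, which states no time term. The 7% precision does not prove a contradiction: away from event rates near 50%, a figure that includes clustering would imply D above 1 and so variation that a common-effect model omits, but its inputs are not given.

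**What to change.** For the primary logistic model and the patient-experience model, name the clustering method. Either include a random department-by-period effect or use cluster-robust errors, in both cases with a t reference on about 7 degrees of freedom. As a sensitivity analysis, report a paired department-level analysis of the eight before-after differences, with case-mix adjustment for patient experience. It should not be presented as equivalent to a random-slope logistic model, because scale and weighting differ.

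No further data are needed. The cost is a wider interval, about 21% from the t reference alone and more if departments do differ, and a slope variance that eight departments will estimate imprecisely.

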**Secondary outcomes**				
Patient experiences	Consumer quality-index questionnaire [29] based on the Consumer Assessment of Healthcare Providers and Systems [30]	3 (before-and-after measurement) *n* = 800	- 3 months; + 9 months and 15 months	Patient
Standardised mortality rate	Routine administrative data of the hospital	Continuously (time series) *n* = 233*	Monthly	Patient
Prolonged hospital stay	Routine hospital administration data	Continuously (time series) *n* = 3268**	Monthly	Patient
Team climate	Team Climate Inventory [18]	2 (before and after measurement) *n* = 132***	- 3 months; + 15 months	Professional or team
Patient safety culture	Hospital Survey on Patient Safety Culture [31,32]	2 (before-and-after measurement) *n* = 132***	- 3 months; + 15 months	Professional
	Safety walk arounds [33,34]	2 (before-and-after measurement) *n* = 8	- 3 months; + 15 months	Department

*Number of patients in the eight departments who died in 2012.

**Number of patients with prolonged stay in 2012 in the eight departments.

***Average number of clinical healthcare providers per department.

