## Discussion

We evaluate the effects of patient safety auditing in hospital care. This study is relevant for hospitals that intend to use early detection of unsafe care and to improve patient safety continuously. Our study provides a better understanding of how auditing can help improve patient safety.

This study has several strengths and limitations. Most patient safety interventions, including auditing, are complex interventions because they often consist of multiple parts (multicomponent) and aim at several levels of the health pyramid (multilevel) and various actors (multitargeted) [44]. Therefore, we set up a mixed-method evaluation study in which we combine qualitative and quantitative measurement instruments to measure several outcomes at different levels: the patient, professional, and departmental levels. We use widely applied and thoroughly studied instruments to measure adverse events, patient experiences, team work, and patient safety culture among healthcare providers [5,18,32,45].

The causal relationship between internal auditing and change in adverse event rates is difficult to identify because of the presence of other hospital initiatives to improve patient safety [44,46]. Therefore, we will carry out a process evaluation to analyse the mechanism and processes responsible for the outcomes of the effect evaluation. We use questionnaires and interviews to study the factors that facilitate or hinder the effectiveness of auditing. This is also important for giving recommendations to other hospitals that want to implement some or all of our audit system.

We will analyse time series data of SMRs and prolonged hospital stay for better evidence of cause-and-effect relationships. Possible underlying secular trends will be detected, and perhaps they will help explain some of the effects [47].

To improve the internal validity by reducing bias, the following actions are taken. To reduce selection bias, patients were randomly selected from the hospital database. All the care personnel in the department who are working in clinical care are invited to fill in the TCI and HSOPS. To prevent participant recall bias, we survey patients 3 months after hospital admission at the latest. The experiences of healthcare personnel and department leaders with the audit system are measured within 2 weeks after the auditing (survey) and 1 month after the revisiting (interviews).

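### The SMR and prolonged-stay model, with 3 pre-audit months and no calendar-time term, does not deliver the secular-trend detection that the Discussion promises

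*Protocol article*

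**What the plan says.** Under Statistical analyses, Patient level, the article states: "We will use a linear mixed model with a Poisson distribution for the SMR and prolonged hospital stay". The purpose is to "compare the rates from baseline to the end of the initial 18-month evaluation period (3 months before and 15 months after auditing"). On covariates it says only: "We will adjust this model for patient and departmental characteristics". No trend, calendar-time or season term is named.

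The Outcomes section says that "the SMR and prolonged hospital stay are generated from the routine administrative hospital data monthly", and Table 4 lists both outcomes as continuous time series. No start date for the series is given. The footnotes to Table 4 give the yearly volumes: 233 ("Number of patients in the eight departments who died in 2012") and 3268 ("Number of patients with prolonged stay in 2012 in the eight departments").

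The Discussion gives these series a special role. They are to be analysed for better causal evidence, and "Possible underlying secular trends will be detected, and perhaps they will help explain some of the effects". It later adds time series analyses, not specified further, as a protection against confounding. It also acknowledges that there are no concurrent controls. Study design and setting places the eight departments' audits between October 2011 and April 2013.

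**The concern.** The design has no control group, and the Discussion itself says that other hospital safety initiatives make causation hard to establish. Table 1 lists changes to the audit system in 2006, 2009 and 2012, the last within the study period. Every other effect outcome in Table 4 is measured at two or three time points. SMR and prolonged stay are therefore the only outcomes that could show a trend already under way before the audit.

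The one analysis specified for them uses 3 months before each audit and 15 after, and contrasts rates without a time term. A slope fitted to 3 monthly points has one residual degree of freedom and covers one quarter of a year. If the rates were already falling, the before-after contrast would contain that fall as well as any audit effect. At stake is whether these two outcomes can carry the causal weight that the Discussion puts on them.

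**Working it through.** **Inputs.** From Table 4: 233 deaths and 3268 prolonged stays in 2012 in the eight departments. From the Patient level analysis text: 3 + 15 = 18 months, which reproduces the stated window. No power, precision or effect size is given for these outcomes, so there is no such figure to reproduce. Assumptions: constant Poisson monthly counts, no overdispersion or autocorrelation, two-sided 5% tests.

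**Monthly counts.** 233/12 = 19.42 deaths (58.25 in 3 months, 291.25 in 15). 3268/12 = 272.3 prolonged stays (817 in 3 months, 4085 in 15).

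**Pre-audit slope from 3 points.** SE = 1/√(m·Σ(t − t̄)²), with m the monthly count and Σ(t − t̄)² = 2.
- Deaths: 1/√(2 × 19.42) = 0.160 per month. As an annual rate ratio around a true value of 1, the 95% interval is exp(±1.96 × 12 × 0.1605) = 0.02 to 44.
- Prolonged stay: 1/√(2 × 272.3) = 0.043 per month; annual interval 0.37 to 2.74.
- With 24 pre-audit months the annual intervals are 0.85 to 1.17 (deaths) and 0.96 to 1.04 (prolonged stay). With 36 months they are 0.92 to 1.09 and 0.98 to 1.02.

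**Spurious effect without a time term.** The midpoints of the two windows are 9 months apart. A pure decline of 5% a year gives about 1 − 0.95^(9/12) = 3.8%; for 10% a year, averaging the monthly rates in each window gives 7.5%. The declines are assumed, since the article gives none.

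SE of the log rate ratio without a trend term: √(1/58.25 + 1/291.25) = 0.144 for deaths; √(1/817 + 1/4085) = 0.038 for prolonged stay. Chance of a significant result when the audit has no effect:

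| Assumed decline per year | Spurious rate ratio | Prolonged stay | SMR |
|---|---|---|---|
| 5% | 0.962 | 17% | 5.8% |
| 10% | 0.925 | 53% | 8.5% |

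**What the 18 months can support if a term is added.** With a step plus one common linear trend on the same 3 + 15 months, the SE of the step is 0.188 for deaths and 0.050 for prolonged stay. The trend SE is 0.0135 and 0.0036 per month. With eight equal departments audited at even intervals over 18 months (an assumption, as exact dates are not given), a model with department and calendar-month effects is of full rank, with step SE 0.205 and 0.055. A segmented model with its own pre-audit slope is a different matter: its effect SE at mid-follow-up is 1.45 for deaths with 3 pre-audit months, against 0.12 with 36.

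**Season.** An assumed ±10% annual wave biases a single audit date by roughly −8% to +10%. Spread over the eight staggered dates assumed above, the pooled bias is about ±1.5%.

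**The case against.** A reader might infer that the secular trend cannot be estimated at all from this window. The document does not support that. A common trend is estimable from the 18 months, and the staggered audits separate calendar time from time since audit across departments. This is usable for prolonged stay and weak for SMR, where the annual trend interval is about 0.73 to 1.37. What remains is that no stated model contains such a term. Moreover, 15 of the 18 months follow the audit, so a common trend fitted in this window could absorb an audit effect that builds up gradually as improvement plans are implemented.

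A reader might also infer that any decline will simply be credited to auditing. That also goes too far. The Discussion names competing initiatives, assigns a process evaluation to them, hedges its sentence on trends, and announces time series analyses without confining them to 18 months. An article condenses, and a longer series may be intended. But the article does fix a window, a contrast and a covariate set, and these do not match its claim.

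Three further inferences should be resisted:
- Seasonal distortion is small once the staggering is taken into account.
- A longer baseline does not halve the interval. That result (0.070 against 0.144 for deaths with 36 months) belongs to a step-only model; a step with trend on 36 pre-audit months gives 0.114.
- Nothing in the article shows that the 3 months before an audit are contaminated by its preparation.

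**Conclusion.** The point holds as a mismatch within the article. The specified model and window do not provide the secular-trend control that the Discussion attaches to these series. Under the assumed declines of 5% and 10% a year, the distortion is a spurious reduction of about 4% and 8%. It matters mainly for prolonged stay and little for SMR, whose false-positive rate stays near nominal because its interval is wide. The figures rest on 2012 volumes and pure Poisson variation. Overdispersion would widen the intervals and lower the false-positive rates of a test that allows for it. Both outcomes are secondary and the record-review primary outcome is not affected, so this should be fixed but is not critical.

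**What to change.** In the Patient level analysis text:

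- State the length of the monthly series, with a longer pre-audit period, for example 24 to 36 months.
- Add calendar-time trend and season terms that use the staggered audit dates.
- Include a level change at the audit and, where the longer baseline supports it, a slope change.
- Add a sensitivity analysis on baseline length. For an audit in October 2011, 36 months reach back to October 2008, across the 2009 redesign in Table 1. With audits every 4 years and a revisit 15 months after each, older months may also carry effects of the previous cycle, and coding may have changed.

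If the series cannot be extended and modelled in this way, withdraw the secular-trend and cause-and-effect statements from the Discussion.

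The cost is modest: "The SMR and hospital stay data are generated from the routine administrative data of the hospital", so the change needs a longer extract, checks of the older data and a few model terms. The statistical price is a wider interval than a step-only model on the same data (deaths, 36 pre-audit months: SE 0.114 with trend against 0.070 without).
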